## Abstract

**Background:**

With persisting maternal and infant health disparities, new models of maternity care are needed to meet the needs of Aboriginal and Torres Strait Islander people in Australia. To date, there is limited evidence of successful and sustainable programs. Birthing on Country is a term used to describe an emerging evidence-based and community-led model of maternity care for Indigenous families; its impact requires evaluation.

**Methods:**

Mixed-methods prospective birth cohort study comparing different models of care for women having Aboriginal and Torres Strait Islander babies at two major maternity hospitals in urban South East Queensland (2015–2019). Includes women’s surveys (approximately 20 weeks gestation, 36 weeks gestation, two and six months postnatal) and infant assessments (six months postnatal), clinical outcomes and cost comparison, and qualitative interviews with women and staff.

**Discussion:**

This study aims to evaluate the feasibility, acceptability, sustainability, clinical and cost-effectiveness of a Birthing on Country model of care for Aboriginal and Torres Strait Islander families in an urban setting. If successful, findings will inform implementation of the model with similar communities.

**Trial registration:**

Australian New Zealand Clinical Trial Registry #ACTRN12618001365257. Registered 14 August 2018 (retrospectively registered).

## Background

Maternal and infant health disparities have persisted between Aboriginal and Torres Strait Islander people and non-Indigenous Australians, with Aboriginal and Torres Strait Islander women having disproportionately higher rates of: maternal mortality (~ 3 times higher) [1]; preterm births (14% vs. 8%); low birth weight infants (liveborn: 12% vs. 6%); and perinatal deaths (12 vs. 9/1000) [2, 3]. Preterm birth is a leading cause of perinatal mortality, serious neonatal morbidity, and moderate to severe childhood disability [4]. It contributes to more than two-thirds of perinatal mortality (fetal loss and neonatal death) [5] and is associated with diabetes, cardiovascular and renal disease in adulthood [6]. Queensland [7] and Western Australian [8] research suggests the majority of perinatal deaths are associated with preterm birth and low birth weight, which in turn are linked to modifiable risk factors: maternal psychosocial stress [9], infections in pregnancy [10], smoking in pregnancy [11], limited maternal education and young maternal age [12]. An Australian Indigenous study found preterm births and perinatal deaths decrease as the number of antenatal consultations increases [13]. Targeting the antenatal period with interventions that are culturally safe and high quality are essential to addressing these health disparities [14–16].

### Birthing on Country

The Australian National Maternity Services Plan [17] identified three priority areas for improving services for Aboriginal and Torres Strait Islander women: 1) developing and expanding culturally competent maternity care; 2) developing and supporting an Aboriginal and Torres Strait Islander maternity workforce; and 3) developing dedicated programs for ‘Birthing on Country’ (best practice maternal and infant services for Aboriginal and Torres Strait Islander women).

An international literature review on Birthing on Country [14] was commissioned by the Australian government who defined Birthing on Country as:‘*Maternity services designed and delivered for Indigenous women that encompass some or all of the following elements: are community based and governed; allow for incorporation of traditional practice; involve a connection with land and country; incorporate a holistic definition of health; value Indigenous and non-Indigenous ways of knowing and learning; risk assessment and service delivery; are culturally competent; and developed by, or with, Indigenous people*’ (p. 5).

The review assisted in identifying the characteristics of successful services [14] and at a national Birthing on Country workshop [18] participants described Birthing on Country as:*‘a metaphor for the best start in life for Aboriginal and Torres Strait Islander babies and their families, an appropriate transition to motherhood and parenting for women, and an integrated, holistic and culturally appropriate model of care for all’* (p. 25).

Aboriginal participants described Birthing on Country as *‘the most powerful thing’* stating it was ‘*about cultural choice’* and ‘*being able to have babies safely on country’* (p. 33):*‘not only bio-physical outcomes ... it’s much, much broader than just the labour and delivery ... (it) deals with socio-cultural and spiritual risk that is not dealt with in the current systems’* (p.24).

Workshop recommendations called for widespread system reform and the development of exemplar models of Birthing on Country in urban, rural and remote areas [18]. Guiding Principles for Developing a Birthing on Country Service Model and Evaluation Framework were subsequently developed and endorsed by the Australian Health Ministers Advisory Council based on the literature and a national workshop [19]. The key components of successful programs that should be integrated in Birthing on Country service models are shown in Table 1. To date, implementation and evaluation of such models has been limited.

**Table 1 Tab1:** Key components of successful, culturally competent Birthing on Country Service Models, reproduced with permission [19]

Birthing on Country Maternity services designed by & delivered for Aboriginal & Torres Strait Islander women & families		
Governance Indigenous control, community development approach, shared vision cultural guidance & oversight		
Philosophy & Overarching Principles Respect for & incorporation of Indigenous knowledge & traditional practice; respect for family & mens’ involvement; partnership approach; women’s business; continuity of carer; connection with country/land; capacity building approach - particularly with training & education; holistic definition of health; choice; evidenced-based clinical practice; social model of health & wellbeing		
*Skill Acquisition, Training & Education* Partnership approach/ two-way learning; appropriately trained & supported; competency based; delivered on-site; career pathway from maternity workers to midwifery; health literacy for women & families	*Service Characteristics* Culturally competent service & staff; community based; specific location; designated ongoing funding; welcoming flexible service focusing on relationships & trust; outreach, transport, child friendly & group sessions; social, cultural, biomedical & community risk assessment criteria; clinical & cultural governance, interdisciplinary perinatal committee; effective IT; integrated services	*Monitoring & Evaluation* Designated funding for monitoring & evaluation; continuous quality assurance; audit activities & recall register
Results Community healing as evidenced by: reduced family separation at critical times, restoration of skills & pride; capacity building in the community; supporting community & family relationships; reduced family violence; increased communication & liaison with other health professionals & service providers; comprehensive, holistic, tailored care; improved maternal & infant health outcomes.		

### Caseload midwifery models

Continuity of care and carer has been identified as an important characteristic of culturally safe care for Aboriginal and Torres Strait Islander women [20]. Caseload midwifery (or midwifery group practice, MGP) is one such model that delivers continuity of midwifery carer throughout pregnancy, labour, birth and the early postnatal period [21]. MGP has been found to significantly improve outcomes for women and babies including reductions in preterm birth and increased satisfaction, breastfeeding, and cost savings [22, 23]. Only 10% of Australian women currently have access to caseload midwifery models, with only a disproportionately small number of Aboriginal and Torres Strait Islander women receiving this model of service delivery [24, 25]. Few services exclusively target Aboriginal and Torres Strait Islanderwomen and many women do not receive continuity of care across the maternity episode; therefore, there is a paucity of research in the area [26].

### The research gap

The main methodological limitations of published interventional studies aimed at improving care and services for Aboriginal and Torres Strait Islander mothers and babies are small sample sizes, short-term evaluations and a lack of an appropriate comparison group [14–16]. Although several studies show promising results, most lack appropriate methodology and/or statistical power. Birthing on Country is a complex intervention that has not yet been rigorously evaluated in an urban Australian setting. The current study will contribute to addressing this knowledge gap by employing a methodologically rigorous study design and participatory research methods to evaluate an urban Birthing on Country continuity of care model for Aboriginal and Torres Strait Islander families in Australia.

## Methods/Design

### Aims

This research project aims to evaluate the feasibility, acceptability, sustainability, clinical and cost-effectiveness, of maternity care for Aboriginal and Torres Strait Islander families in South East Queensland. Specifically, this study aims to:Restructure services to incorporate the key characteristics of a Birthing on Country Service Model of maternity services for Indigenous women in an urban setting, including an enhanced midwifery group practiceConduct an evaluation of the restructure using a prospective cohort studyUtilise participatory action research methods to ‘fine tune’ the restructure of servicesDetermine if women receiving this new model have improved maternal and infant health outcomes when compared to women receiving other models of care and baseline dataDetermine the acceptability and sustainability of this new model of careEvaluate the economic impact of this modelExplore the pregnancy and early parenting (six months postnatal) experiences of 20 women using an ethnographic approach accessing different models of care.

### Study setting

South East Queensland comprises one of the largest and fastest growing Aboriginal and Torres Strait Islander populations of Australia [27]. The Birthing in Our Community service, launched in 2013, is a new model of care informed by the Birthing on Country literature and Guiding Principles. This model of care is available to women having Aboriginal and Torres Strait Islander babies at the Mater Mothers’ Hospital (MMH), one of the largest tertiary maternity hospitals in Australia. Birthing in Our Community is conducted in partnership with two local Aboriginal Community Controlled Health Organisations: the Institute for Urban Indigenous Health (IUIH) and the Aboriginal and Torres Strait Islander Community Health Service Brisbane Limited (ATSICHS). The partnership is underpinned by a Memorandum of Understanding and Statement of Commitment to share resources to redesign maternal and infant health services. Service characteristics were based on the literature review [14] and the workshop report [18] as well as tailoring to the local context following recommendations from a World Café attended by 60 local stakeholders [28]; which resulted in the partnership. The overarching aim of the Birthing in Our Community partnership is to close the gap in Aboriginal and Torres Strait Islander maternal and infant health outcomes, particularly preterm birth, through the translation of evidence-based strategies into the Birthing in Our Community program.

In developing the evaluation of the Birthing in Our Community program we aimed to compare outcomes for mothers and infants with a similar cohort of women receiving standard care. After reviewing the statistics from across South East Queensland, the most appropriate comparison cohort was women attending the Royal Brisbane and Women’s Hospital (RBWH) where senior managers and researchers agreed to collaborate on a joint project and funding submission. However, as the funding was being awarded, the RBWH also changed their model of care (2013) for Aboriginal and Torres Strait Islander women through the Ngarrama Indigenous Maternity Service and it is no longer standard care. The Ngarrama Service is a government-funded midwifery continuity of care service for women having an Aboriginal and/or Torres Strait Islander baby/ies and planning to birth at the RBWH (located fewer than six kilometres north of the MMH). Thus we have agreed to evaluate both new services, Birthing in Our Community and the Ngarrama Service, and will compare them to each other, and to women receiving standard care and to baseline data from both hospitals. (Note: not all women having Aboriginal and Torres Strait Islander babies at both MMH and RBWH access the Indigenous-specific models of care hence the concurrent comparison with standard care). Table 2 outlines the components of the different models of care available to women having Aboriginal and Torres Strait Islander babies at the MMH and RBWH. For the first time, researchers will test the effectiveness of caseload midwifery in an urban setting where 100% of the midwives’ caseload are women having Aboriginal and Torres Strait Islander babies receiving care across the maternity continuum (antenatal, birth, until 6 weeks postnatal).

**Table 2 Tab2:** Models of care available to Aboriginal and Torres Strait Islander families at study sites

Birthing in Our Community (Group 1)	Standard Care (Groups 2, 5)	Ngarrama Maternity Service (Group 4)
Indigenous governance (operating through a Steering Committee) functioning in accordance with Terms of Reference and underpinned by a MOU A community-based Midwifery Group Practice (MGP), which provides continuity of care to enrolled women throughout pregnancy, birth and up to six weeks postnatally Care is provided according to hospital guidelines and protocols in the home and at community venues where regular cultural and education days are held 24/7 access to caseload midwife who works in MGP of 4FTE on annualised salary with each woman allocated a primary midwife. Midwife support during birthing is likely to be by a known midwife. Location for birth is the Birth Suite (no homebirth or Birth Centre services provided)^a^ Indigenous Maternal Infant Health/ Family Support Workers and Indigenous student midwives work with the caseload midwives to provide culturally tailored care Referral to and integration with Indigenous community support agencies as required; All women are offered a formal handover to child health services with other referrals as required (e.g. paediatric, allied health) Clinical and cultural supervision for staff.	Antenatal care may be received from community based general practitioner, hospital based midwives or doctors who rotate throughout the service on rosters. Midwife support during birthing is likely to be by a midwife the woman has never met. Postnatal care or phone call from a rostered community midwife might take place if the woman meets the criteria for early discharge—before 48h for vaginal birth and 72h for caesarean section usually for up to less than two weeks No 24/7 access to MGP midwife but can call hospital birthing suite in emergency Location for birth same as other groups for the hospitals	A hospital-based Midwifery Group Practice (MGP) with a community clinic one day a week, which provides continuity of care to enrolled women throughout pregnancy, birth and up to six weeks postnatally. Care is provided according to hospital guidelines and protocols, regardless of setting (women’s homes, community venues or hospital) 24/7 access to MGP midwives who work in a small team and are on annualised salary with each woman allocated a primary midwife. Midwife support during birthing is likely to be by a known midwife. Location for birth may be in the Birth Suite or the co-located Birth Centre (eligibility criteria apply); Access to Cultural Capability Officers of the regional (Metro North) Aboriginal and Torres Strait Islander Health Unit who provide additional cultural guidance and support.
Indigenous Liaison Officers are based in the hospitals to strengthen culturally responsive care and support Access to medical staff, allied health professionals, social workers, child safety officers and other professionals (e.g. diabetic educator) as required Discharge letter to referral doctor and referrals to community support agencies as required		

^a^Despite community recommendations for an Indigenous Birthing Centre, funding has not yet been secured

### Study design

This study underwent peer review by the funding body, the National Health and Medical Research Council*.* This study will consist of a prospective cohort study comparing:*Maternal and infant health outcomes*: women booked to receive maternity care through MMH or RBWH, by model of care and Aboriginal and Torres Strait Islander status of baby and/or mother (see Table 3). Routinely collected clinical outcomes for mothers and infants will provide data on the effectiveness of the programs since they commenced in late 2013 and be compared across groups for the duration of the study (ending in 2019), and to baseline data for both hospitals (2009–2013). Infant assessments will be undertaken at two and 6 months postnatally for Groups 1 and 4.*Service acceptability, effectiveness and cost-effectiveness:* Maternal surveys will be undertaken as early as possible antenatally (~ 20 weeks and 36 weeks antenatally, two and six months postnatally). An ethnographic component will also explore the pregnancy and early parenting (to six months postnatal) experiences of ~ 20 women from each Birthing in Our Community and the Ngarrama Service using a longitudinal, ethnographic approach: ‘Tell My Story’ substudy. Cost-effectiveness analysis will be conducted from the broader ‘societal’ perspective which will include not only the cost to the hospital (Routine data) but the cost to the women (Women’s surveys) and partner organisations (Routine data).*Service sustainability and feasibility:* Staff perspectives and experiences will be compared across the services to determine the sustainability and feasibility from a workforce perspective.

**Table 3 Tab3:** Timeline of groups by model of care and research data available

Year	2009	2010	2011	2012	2013	2014	2015	2016	2017	2018	2019
Groups by model of care						Group 1: Birthing in Our Community, MMH (Indigenous)					
	Group 2: Standard care, MMH (Indigenous)										
	Group 3: Standard care, MMH (Non-Indigenous)										
						Group 4: Ngarrama Indigenous Maternity Service, RBWH (Indigenous)					
	Group 5: Standard care, RBWH (Indigenous)										
	Group 6: Standard care, RBWH (Non-Indigenous)										
Research data (Groups)	*Baseline*					*Study period*					
	Routine Data (2, 3, 5, 6)					Routine Data (1–6)					
						Women’s Surveys (1, 2, 4, 5)					
						Tell My Story (1, 4)					
						Infant Assessments (1, 2, 4, 5)					
						Staff Interviews (1, 4)					

Birthing in Our Community is a complex intervention with multifaceted components; identifying its ‘active ingredients’ is vital to evaluating effectiveness and replicating the intervention in other settings [29]. As with the Ngarrama Service, an appropriate monitoring and evaluation framework [29, 30] is needed that enables all stakeholders to understand not only what components are integral to success or failure but why these components are so important and influential. A Program Logic Model will be used for the monitoring and process evaluation to assess if the services are being implemented as planned [28]. Program logic is essentially a conceptual ‘road map’ that presents the thinking/theory behind the expected outcomes of research activities.

A mixed-methods research design has therefore been selected as the most appropriate to achieve these goals, with equal weight given to both qualitative and quantitative approaches. Incorporating participatory action research [31] (PAR), as recommended for Indigenous research [32], will allow the research team to be responsive to evaluation findings throughout the duration of the study. In line with a PAR approach, the IBUS research team will meet regularly to discuss relevant issues and collaboratively plan research-related activities, with regular reflections on previous steps, progress to date, and future expectations/aspirations [31]. Regular Steering Committee meetings provide a mechanism (Birthing in Our Community only) enabling timely feedback and regular reporting to key stakeholders.

### Study participants

#### Inclusion/exclusion criteria

##### Women’s surveys, Tell My Story and Infant Assessments

Women are eligible to participate if they:Are having an Aboriginal and/or Torres Strait Islander baby;Receive their maternity care through the Birthing in Our Community program and are planning to birth at the MMH (Group 1); receive their maternity care through the Ngarrama Indigenous Maternity Service and are planning to birth at the RBWH (Group 4); receive standard maternity care and birth at the MMH or RBWH (Groups 2 & 5); andConsent to participate.

Women are not eligible to participate if they:Have been transferred into the RBWH or the MMH from out of area for high-level specialist services or received no antenatal care.

Infants are eligible if:They are Aboriginal and/or Torres Strait Islander and their mothers received care through either of these hospitals and were recruited to the study.

##### Routinely collected clinical and costing data (Groups 1–6)

Women and infants will be excluded if they have been transferred into the RBWH or the MMH from out of area for high-level specialist services or received no antenatal care.

##### Staff surveys, interviews, and focus groups (Groups 1–6)

Staff are eligible to participate in the staff surveys, interviews and focus groups if they have been involved in the planning and/or provision of maternity care services for Aboriginal and Torres Strait Islander families in South East Queensland during the study period; and consent to participate.

#### Power and sample size

This study has been powered to detect changes in clinical outcomes and the number of women accessing care per annum in each program [33]. During the 3.5-year recruitment period, we will aim to access routinely collected data for approximately 420 women at MMH, and 350 from RBWH (based on an estimated 20% attrition rate). The change in outcomes has been estimated based on changes seen in the Townsville Mums and Bubs program that reported a reduction in preterm birth [34] (Table 4).

**Table 4 Tab4:** Power calculations with *n* = 350 in each arm + 20% for attrition

Outcome	From %	To %	No./ cohort	Power
Proportion of women who attend ≥ 5 antenatal visits	81.0	90.0	261	0.924
Proportion of women who were smoking after 20 weeks	42.0	31.0	318	0.858
Preterm birth < 37 weeks pregnancy	16.0	9.0	350	0.801
Exclusive Breast feeding at discharge (2007–09 Mater data)	78.0	88.0	240	0.942

The sample size for the ethnographic component of the study (‘Tell My Story’) will involve a smaller group of women from each cohort. The project aims to recruit up to 25 women from each cohort, which factors in a 20% attrition rate (25*.8 = 20).

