#### Routinely collected data (Groups 1–6)

We are seeking a waiver of consent to access routinely collected data for the all cohorts of women in order to satisfactorily answer the outcome measures. This will include both clinical and costing data. For women who participate in the IBUS surveys, consent will be sought to link IBUS survey data to routinely collected data. Initially the data will be collected in an identifiable form so we can be assured that data from different sources can be merged with each participant given one unique identifier. Once this is completed all identifiable data (e.g. name, address) will be removed and kept only in the participant log, which will be used to contact participants at different time points.

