### Data analysis and management

#### Quantitative

Clinical data will initially be collected in a re­identifiable form (via the unique patient identifier) so that it can be linked with data obtained from other sources (e.g. surveys), to enable the economic analyses to be undertaken. Once merged, identifiers will be removed and only the coded number will remain.

Quantitative analyses will compare the difference in clinical outcomes between Birthing in Our Community (intervention), the Ngarrama Service (concurrent control), standard care (historical and concurrent control), and also non-Indigenous women and babies (historical and concurrent control) at MMH and RBWH.

Data on all women attending either hospital during the study period will be extracted. Women transferring in from other hospital or rural and remote areas for higher-level services (variable available), and those with no antenatal care will be excluded from analysis. Analyses will be by birth model of care and women with multiple births and their infants with identified fetal anomaly will be excluded from analysis unless noted otherwise.

Initial bivariate analysis will investigate possible differences between the cohorts for baseline socio-demographic (socio-economic status), and clinical characteristics (e.g. age, parity, body mass index, smoking, obstetric history) that could affect outcome measures. Dependent on data type, analysis will be undertaken using an independent samples t-test, Mann-Whitney U test or chi-squared test. Outcome measures will be presented using relative risks with 95% confidence intervals. Multivariate logistic, linear regression models and propensity score matching will be used to adjust for confounders. Longitudinal outcomes (e.g. breastfeeding) will be analysed with generalized estimating equations to account for the correlation between observations repeated in the same person. To understand the mechanism or process that underlies the effect of model of care on outcomes, mediation analysis will be conducted to identify if and to what extent the other variables explains the relationship. All withdrawals, losses to follow-up, and deaths will be reported. Analysis will be performed with SPSS Version 22.0/Stata 14.0 and statistical significance will be at the 0.05 level.

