## Discussion

This study will test the impact of two maternity models of care for one of Australia’s highest priority health populations: Aboriginal and Torres Strait Islander mothers and babies. The model and economic impact assessment have been derived from international best-practice and service evaluations in Australia and our study has the statistical power to detect a difference in preterm birth. The multi-agency approach to implementing a Birthing on Country Service Model at one site has been recommended in Aboriginal and Torres Strait Islander policy documents and will be evaluated. The economic impact assessment aims to quantify the impact of the model by articulating the process by which research leads to impacts on the end-user and/or the broader community. If the model is successful and demonstrates a good return on investment, we will have developed and evaluated a culturally safe service model transferable to other settings for trialling in a broader context.

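### The stated targets (420 and 350 women) do not match Table 4's 350 per arm plus 20%, so its power figures do not describe the planned numbers

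*Protocol article*

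**What the plan says.** The text under Power and sample size sets the aim of obtaining routinely collected data for "approximately 420 women at MMH, and 350 from RBWH (based on an estimated 20% attrition rate"). Directly below it, Table 4 is captioned "Power calculations with *n* = 350 in each arm + 20% for attrition". Its row "Preterm birth < 37 weeks pregnancy" gives 16.0% falling to 9.0%, 350 per cohort and power 0.801. The other rows give powers of 0.924 (five or more antenatal visits), 0.858 (smoking after 20 weeks) and 0.942 (exclusive breastfeeding at discharge). The same section applies 20% attrition to the Tell My Story substudy as 25 × 0.8 = 20.

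Three other places bear on this. The section on routinely collected data says "We are seeking a waiver of consent to access routinely collected data for the all cohorts of women". The Quantitative analysis section says "statistical significance will be at the 0.05 level". The Discussion says "our study has the statistical power to detect a difference in preterm birth".

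**The concern.** The caption gives both arms the same analysed number and the same attrition allowance. The text gives 420 to one hospital and 350 to the other, and attaches the 20% to both. MMH's 420 is the caption's 350 with 20% added, whereas RBWH's 350 is the caption's number with nothing added. As printed, the two statements cannot describe one plan.

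Preterm birth has the largest required number in Table 4 and the lowest power. At 0.801 it has no room to lose women and stay at 80%. It is also the outcome for which the Discussion claims adequate power. If the targets are recruitment numbers that then lose 20%, that claim rests on a power the plan would not reach.

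The 20% is also hard to place. It is attached to routine data, which are to be obtained under a consent waiver. The four primary outcomes are listed for all groups, and Table 3 gives Groups 3 and 6 routine data only. Survey drop-out would therefore not obviously reduce the numbers for these outcomes.

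**Working it through.** **Inputs.** Rates, number per cohort and stated powers come from Table 4. Targets and the 20% come from the text above it. The 0.05 level comes from the Quantitative analysis section. Two-sided testing is assumed, because the protocol does not state it; for preterm birth at 350 per arm, two-sided testing reproduces 0.801, while one-sided gives 0.877.

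**Formula.** Pooled-variance normal approximation for two proportions, without continuity correction:

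- p̄ = (n₁p₁ + n₂p₂)/(n₁ + n₂)
- SE₀ = √[p̄(1 − p̄)(1/n₁ + 1/n₂)]
- SE₁ = √[p₁(1 − p₁)/n₁ + p₂(1 − p₂)/n₂]
- power = Φ[(|p₁ − p₂| − 1.96 SE₀)/SE₁]

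**Step 1: reproduce Table 4.** For preterm birth at 350/350, p̄ = 0.125, SE₀ = 0.0250 and SE₁ = 0.0249. Then (0.07 − 1.96 × 0.0250)/0.0249 ≈ 0.845, and power = 0.801. At 350 per arm the same formula also returns 0.924, 0.858 and 0.942 for the other three rows. All four stated powers are therefore those for 350 analysed per arm.

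**Step 2: apply the stated attrition to the stated targets.**

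- 350 × 1.2 = 420, the MMH target; RBWH's 350 has no such factor.
- 420 × 0.8 = 336 and 350 × 0.8 = 280, both below 350.
- To retain 350 after a 20% loss: 350/0.8 = 437.5, so 438.

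**Step 3: power at each analysed number.** With unequal arms the result depends slightly on which arm has the higher rate, so a range is given.

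| Reading | Analysed | Preterm-birth power |
|---|---|---|
| Table 4 as stated | 350 / 350 | 0.801 |
| Text targets, then 20% lost | 336 / 280 | 0.741–0.750 |
| 420 recruited in both arms, then 20% lost | 336 / 336 | 0.785 |
| 438 recruited in both arms, then 20% lost | 350 / 350 | 0.801 |
| Text targets already net, or no attrition | 420 / 350 | 0.831–0.837 |

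For 336/280 with 16% in the larger arm, p̄ = 0.1282, SE₀ = 0.02705 and SE₁ = 0.02632, so (0.07 − 1.96 × 0.02705)/0.02632 ≈ 0.645 and power = 0.741.

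**Step 4: the other primary outcomes at 336/280.** Smoking is about 0.81 (stated 0.858), antenatal visits about 0.885 (stated 0.924) and breastfeeding about 0.91 (stated 0.942). Only preterm birth falls below 0.80.

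**Step 5: sensitivity to the formula.** For preterm birth at 336/280, the unpooled version gives 0.740–0.758, the arcsine version 0.752 and the continuity-corrected version 0.70–0.71. Each is lower than the same method's value at 350/350 (0.804, 0.807 and 0.767).

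**The case against.** A reader might infer that the study's preterm-birth power simply is 0.74–0.75 and that the study is underpowered. The documents do not support that as a fact, for three reasons.

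First, the sentence speaks of women whose data will be accessed, with "based on an estimated 20% attrition rate" in brackets. It can be read as saying that 420 and 350 are what remains after attrition. Both hospitals then reach 350 and there is no shortfall. The match 420 = 350 × 1.2, and the 25 × 0.8 = 20 usage in the same section, favour reading them as numbers before attrition, but they do not settle it.

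Second, if attrition does not apply to waivered routine data, the relevant figure is about 0.83–0.84. That is above the stated 0.801, and the Discussion's claim would stand.

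Third, the protocol never says that Table 4 compares MMH with RBWH. The From and To columns, the effects taken from an earlier program, and a breastfeeding baseline from 2007–09 Mater data look as much like change from baseline. The plan includes comparison with 2009–2013 data, whose size is not given. If that baseline held, say, 700 women (purely an assumption), 280 followed women would give about 0.84 and 336 about 0.89.

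The targets are also approximate aims, and the analysis section says that data on all women attending either hospital will be extracted, so they need not be ceilings. Nor is 0.801 a miscalculation.

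All of this stands, and it makes the shortfall conditional. It does not remove the inconsistency: a net reading contradicts the caption, a before-attrition reading leaves RBWH without the allowance, and 0.801 belongs to neither pair of numbers. A condensed article may leave detail elsewhere, but here two printed statements disagree.

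**Conclusion.** The section is inconsistent as written. Table 4's powers are right for 350 analysed per arm but do not correspond to the stated targets on either reading. Taking MMH versus RBWH as the contrast, two-sided 0.05 and Table 4's rates, preterm-birth power is about 0.74–0.75 if the targets then lose 20%, some 5 to 6 percentage points below the stated figure. It is about 0.83–0.84, some 3 to 4 points above it, if they do not. The documents do not say which applies.

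Separately, adding 20% does not offset a 20% loss: 420 in both arms would retain 336 each and give 0.785. That part is small.

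This is a reporting correction of moderate weight. It changes no outcome or analysis, but it touches the figure behind the Discussion's power statement.

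**What to change.** In Power and sample size:

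1. Name the contrast that Table 4 powers (hospital against hospital, new model against standard care, or new model against baseline) and give the number in each arm.
2. Say whether 420 and 350 are before or after attrition.
3. Say whether the 20% applies to routine data obtained under the waiver, or only to the surveys and infant assessments.
4. Restate all four powers at the resulting analysed numbers. For MMH versus RBWH, preterm birth is 0.74–0.75 at 336/280 or 0.83–0.84 at 420/350.
5. Wherever attrition applies, inflate by n/(1 − 0.2), so that 350 becomes 438, or quote the power for the number retained.
6. Make the Table 4 caption and the Discussion's power sentence agree with the restated figures.

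The cost is a few sentences and a revised table. No extra women are needed to report the power correctly, and no data collection or analysis changes.
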